### 13.5 Efficacy analyses

The primary analysis will be based on all patients who entered phase II of the trial (ITT population). Multiple imputation methods with mSASSS score at baseline as covariate (SAS procedure PROC MI) will be applied to deal with missing radiographs in the primary analysis. The Mann-Whitney test will be used to compare the primary outcome (change in the mSASSS score) between the treatment groups. Cumulative probability plots of will be built to visualise the finding.

In a secondary analysis the Mann-Whitney test will be used to compare radiographic progression in the subgroup of patients with complete sets of radiographs. A likelihood approach will be applied to deal with missing data in secondary outcome parameters assessed at multiple time points (Molenberghs G., Kenward M.G. Missing data in clinical studies. Chichester: John Wiley & Sons; 2007). For that reason linear mixed models (SAS procedure PROC MIXED) will be applied to compare means of secondary outcome parameters over time. Time and group, (time\*group) will be included in these models as fixed effects and patient-ID as a random parameter (included in PROC MIXED via the repeated statement with type = un for an unstructured covariance matrix). In the case of skewed data PROC MIXED will be applied to log-transformed parameter (CRP) or non-parametric tests (Mann-Whitney test, non-parametric analysis of covariance) will be applied (e.g., for biomarker data). Spearman rank correlation and non-parametric analysis of covariance will furthermore be used to investigate the association between radiographic progression and biomarkers of inflammation and bone/cartilage turnover (Bathke A, Brunner E. A nonparametric alternative to analysis of covariance. In: Akritas MG, Politis DN eds. Recent advantages and trends in nonparametric statistics. Amsterdam: Elsevier Science and Technology 2003: 109-20).

Nonresponder imputation for missing response data and chi-square tests will additionally be applied to compare response rates. Two-sided p values < 0.05 will be considered to be statistically significant.

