|                 | 
n=190; assuming a 10% screening failure rate approximately.
 
To be allocated to trial:
n=170 patients with active AS despite treatment with NSAIDs alone will be included in the phase I of the trial and treated with Golimumab. Only patients with good clinical response after 12 weeks of treatment will be enrolled in the phase II of the trial. It is assumed that approximately 60% (n=100) of patients included in phase I will continue in the phase II of the study, considering that elevated CRP at baseline is currently the best response predictor for TNF-blocker therapy.
 
To be analysed:
n=100 (n=50 in each group) patients will enter phase II of the trial (intention-to-treat population - ITT) after 1:1 randomization.
 
Statistical analysis:
 
Efficacy:
Efficacy of the therapy in reduction of radiographic spinal progression will be assessed by the modified Stoke Ankylosing Spondylitis Spine Score (mSASSS). mSASSS is a radiographic score measuring structural changes in the lumbar and cervical spine. Images will be scored by 2 trained readers in a blinded manner that allows the open-label (although randomized) design of the trial.
The primary efficacy endpoint will be radiographic spinal progression assessed by the change in the mSASSS score over two years of therapy in both groups. The primary analysis will be based on the intention-to-treat population, a secondary one in patients with complete sets of radiographs at two time points. A two-sided Mann-Whitney U-test will be applied to compare the mSASSS progression between both treatment groups in both analyses.
 
Safety:
Safety outcome will include absolute number and percentage of patients who experienced adverse events (AE), serious AE, AE of interest (infections, malignancies, gastrointestinal events: ulceration, bleeding, perforation, gastric outlet obstruction; thrombotic cardiovascular events: myocardial infarction, stroke, pulmonary artery embolism, peripheral arterial of venous thrombosis; renal and hepatic function deterioration), as well as a proportion of patients who discontinued the study because of AEs.
In order to address possible long-term safety issues related to long term use of NSAIDs a safety Follow-Up Visit will be performed 3 months after discontinuation of the study treatment (either week 108 or the last study visit in the case of early discontinuation).
Safety population will include each patient who received at least one dose of Golimumab with or without Celecoxib. Statistical comparisons will be based on event rates per 100 patient years of exposure. Rates will be compared by exact Poisson methods.
 
Secondary endpoint(s):
Mann-Whitney U-test, linear mixed models, and Chi-square test will be used in order to evaluate differences in the secondary outcome parameters between treatment groups.
 |

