### *X-rays of the spine*

X-rays of the lumbar and cervical spine (lateral views) will be performed during screening only if there were no image performed within the previous 24 months. Those images are central for the conduct of the study (primary outcome; inclusion criterion #5b and exclusion criterion #10). Quality of the x-rays should allow this assessment, i.e., images should be available in electronic form or as x-ray film (no paper printouts). If no images fulfilling these criteria are available, X-rays of the cervical and lumbar spine should be performed during the screening period. A second set of X-rays of lateral cervical and lumbar spine must be performed at Week 108, or in case of an early termination (ET) if the patient reached at least Week 84..

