### 13.7 Methods against Bias

There will be three different methods avoiding possible bias:

- 1) Randomization at Week 12: subjects who present a good response to TNF-blocker therapy will be randomized 1:1 by a FDA 21 part 11 compliant software tool (SecuTrial) of the Coordinating Center for Clinical Studies of the Charité Berlin (KKS Koordinierungszentrum für Klinische Studien) in order to receive Golimumab plus continuous treatment with Celecoxib vs. Golimumab alone. This study protocol allows the inclusion of patients in whom the baseline radiographic examination of the spine was done up to two years prior to screening. A possible bias caused by differences in the length of the time intervals between the baseline and the week 108 radiographic examination of the patients will therefore be controlled for by randomization. Prior to randomization patients will be stratified by time period between radiographic examination used as baseline radiographic examination and the visit at week 12. Three months intervals (0-3, 4-6 etc. months) will be considered to build up these strata. Block randomization stratified by these strata will be used. This method will therefore balance the treatment groups for an important factor with the potential to influence the outcome. Of note, only subjects who are eligible for randomization represent the target population of the study.
- 2) Blinded and independent reading of the spinal radiographs: the primary outcome (radiographic progression) will be assessed centrally by two trained readers blinded to all data including treatment allocation and also to the time points the x-rays were taken.
- 3) A possible bias caused by patients with missing radiographs at follow up (e.g. dropouts) is considered in the statistical analysis (see 13.5).

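### The primary Mann-Whitney test uses neither baseline mSASSS nor the film-interval factor that stratifies randomisation: it is valid, but gives up precision, mostly from baseline mSASSS

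*Protocol*

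**What the plan says.** The primary test is fixed in two places. Protocol section 13.5 states: "The Mann-Whitney test will be used to compare the primary outcome (change in the mSASSS score) between the treatment groups". The synopsis (section 2) says the same for the imputed intention-to-treat analysis and for the complete-radiograph analysis: "A two-sided Mann-Whitney U-test will be applied to compare the mSASSS progression between both treatment groups in both analyses". Neither mentions a stratum or a covariate.

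Three other statements bear on this.

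- **Film age.** Under section 6.7, spinal X-rays "will be performed during screening only if there were no image performed within the previous 24 months". The baseline film can therefore be up to two years old at screening.
- **Randomisation.** Section 13.7 stratifies by the time from that film to the week 12 visit: "Three months intervals (0-3, 4-6 etc. months) will be considered to build up these strata", and "Block randomization stratified by these strata will be used". It says this will "balance the treatment groups for an important factor with the potential to influence the outcome" and that bias from unequal intervals "will therefore be controlled for by randomization".
- **Baseline mSASSS.** In the primary analysis it appears only in the handling of missing films: "Multiple imputation methods with mSASSS score at baseline as covariate (SAS procedure PROC MI) will be applied".

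Section 13.5 also cites non-parametric analysis of covariance, but for skewed secondary data and for the relation between biomarkers and progression, not for the primary comparison of arms.

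**The concern.** The plan treats two pre-randomisation variables as informative about progression and then leaves both out of the primary comparison. Baseline mSASSS is trusted to predict missing change scores. Film interval is trusted to define the randomisation strata. A test that ignores predictors of the outcome leaves their variation in the error term. When randomisation was stratified on one of them, the unstratified test is also, in principle, slightly conservative.

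At stake is precision in a trial that expects to randomise about 100 of 170 enrolled patients and follow them for 96 weeks. Both variables will be on file for every randomised patient with a usable baseline film. Because the protocol names the primary test, an adjusted analysis chosen after the data are seen would be post hoc.

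**Working it through.** **Inputs from the protocol.** Section 13.8: change 1.7 (SD 2.8) in the control arm and 0.2 (SD 1.6) in the combination arm, difference 1.5, two-sided alpha 0.05, power 80%, variance increase from imputation below 25%. Synopsis: 50 per arm. Sections 6.7 and 13.7: film window and strata. **Assumed, because the protocol gives no figure:** R², the share of the variance of change explained by the covariates.

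**1. Reproduce the plan's figure.** SE = √[(2.8² + 1.6²)/n] = √(10.40/n), with Welch-Satterthwaite degrees of freedom and power from the noncentral t distribution. Power is 79.4% at n = 37 and 80.5% at n = 38, so 38 per group reproduces.

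**2. Add the imputation allowance.** 10.40 × 1.25 = 13.00. The smallest n per arm for 80% power is 47; simple scaling, 38 × 1.25 = 47.5, gives 48. At 50 per arm, SE = √(13.00/50) = 0.510 and power is 82.8%. The planned 100 patients are sufficient for an unadjusted test.

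**3. Allow for adjustment.** The variance becomes 13.00 × (1 − R²).

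| Assumed R² | Sum of variances | SE at 50 per arm | Power at 50 per arm | n per arm for 80% |
|---|---|---|---|---|
| 0 | 13.00 | 0.510 | 82.8% | 47 |
| 0.05 | 12.35 | 0.497 | 84.6% | 45 |
| 0.10 | 11.70 | 0.484 | 86.5% | 43 |
| 0.20 | 10.40 | 0.456 | 90.1% | 38 |
| 0.30 | 9.10 | 0.427 | 93.5% | 33 |

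At R² = 0.20 the adjustment exactly cancels the imputation allowance (1.25 × 0.80 = 1).

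**4. How much of this is film interval?** Film to week 12 runs from 12 weeks (2.8 months) to 24 months + 6 weeks + 12 weeks (28.1 months), a range of 25.4 months or 2.115 years, which gives up to 10 three-month strata. If intervals are uniform (assumed), their variance is 2.115²/12 = 0.373 years². If progression is linear (assumed), the control rate is 1.7/2 = 0.85 per year. Interval then contributes 0.85² × 0.373 = 0.269, and 0.269/2.8² = 3.4% of control-arm variance. In the combination arm, 0.1² × 0.373 = 0.0037, and 0.0037/1.6² is about 0.1%. An R² of 0.02 to 0.04 takes power from 82.8% to between 83.5% and 84.3%, so interval alone is worth about 1 to 1.5 points at most. Anything larger must come from baseline mSASSS.

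**5. Check with rank tests.** Simulation: 50 per arm, variance +25%, blocks of 4 (assumed) in 10 interval strata, scores in 0.5 steps, interval R² 0.04 in both arms, 3,000 runs per scenario.

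| Scenario | Mann-Whitney | Van Elteren, 10 strata | Rank ANCOVA |
|---|---|---|---|
| Normal, baseline R² 0 | 80.7% | 78.9% | 81.8% |
| Normal, baseline R² 0.10 | 80.4% | 78.4% | 84.8% |
| Normal, baseline R² 0.20 | 79.6% | 77.9% | 87.0% |
| Skewed, baseline R² 0 | 84.8% | 87.7% | 87.6% |
| Skewed, baseline R² 0.10 | 80.5% | 79.6% | 87.6% |
| Skewed, baseline R² 0.20 | 78.3% | 77.2% | 89.4% |

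Type I error was about 3.6% to 5.6% for all three tests across scenarios. Stratifying the rank test alone usually changed power by 0 to −3 points; the exception was the skewed scenario with interval as the only predictor. Interval alone gained 1.2 points (normal) and 2.8 points (skewed) with rank ANCOVA, with its share set higher than step 4 gives for the combination arm.

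**6. Which interval may be used.** Film to week 12 is known before randomisation. The actual film-to-film interval is not: at early termination the second film may be taken from week 84 (sections 3, 6.1 and 6.7). Section 6.6.1 also withdraws combination-arm patients after a celecoxib interruption of more than 4 weeks, a rule that cannot apply to the control arm. Film-to-film time can therefore depend on arm.

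**The case against.** The best defence is that nothing here is an error. The trial was sized for an unadjusted comparison and the sizing reproduces. Stratified allocation does address bias from unequal film ages, as section 13.7 says. An unadjusted rank test is simple and legitimate. All of that stands.

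A reader might infer that the primary test is invalid, biased or underpowered. The documents do not support that: simulated type I error is close to nominal, and power is 82.8% even with the full variance allowance. A reader might also infer that the ignored strata are the main fault, because the mismatch between sections 13.5 and 13.7 is so visible. Step 4 shows that they account for little. Nor is chance imbalance in baseline damage a separate bias. If half of the 100 patients had syndesmophytes (an assumed share), the arms would differ by 10 points or more in about 32% of randomisations, but the test's type I error already covers such imbalance.

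The size is open to challenge too. The R² values are assumed, and one R² is applied to both arms although the plan expects almost no mean progression in the combination arm. Inclusion criterion 5 requires elevated CRP or a syndesmophyte in every patient, which narrows the risk range and could lower R². The figures in step 3 are t-test approximations. These points limit the magnitude but not the direction.

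The defence is weaker in saying that this can be left to the SAP. Supportive analyses can be, but the primary test is named in the protocol, and a supportive adjusted analysis would not recover the precision of the primary one.

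**Conclusion.** The point holds as one of efficiency. The primary test omits a baseline value that the plan already uses for imputation and the factor on which it stratifies randomisation. Validity and the planned 80% power are not in question.

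At 50 per arm with variance +25%, adjustment is worth about 2 points of power at R² 0.05, about 4 at 0.10 and about 7 at 0.20, starting from 82.8%. These gains rest on the assumed R², on the t-test approximation and on the SDs in section 13.8; the rank-test simulation agrees in direction. Nearly all of the gain depends on baseline mSASSS. The omission is certain, but its size cannot be settled from the protocol.

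**What to change.** Before database lock, and preferably before any mSASSS result is seen by arm, since the trial is open-label:

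1. Make the primary test the non-parametric (rank) analysis of covariance already cited in section 13.5. Use mSASSS change as outcome, arm as factor, and two covariates: baseline mSASSS and the time from baseline film to week 12, entered as a continuous variable. State how results are pooled across imputations, and include the interval in the imputation model so that it matches the analysis.
2. Do not adjust for the actual film-to-film interval, for the reason in step 6. Do not substitute a van Elteren test: over about 10 sparse strata it usually gained nothing, and a version with collapsed strata was not tested.
3. Report a covariate-adjusted mean difference with 95% CI beside the test. The 1.5-unit relevance threshold in section 13.8 is a mean difference, and a rank p-value cannot be read against it.
4. Keep the unadjusted Mann-Whitney as a sensitivity analysis.

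The cost is amendment wording in the synopsis and section 13.5, with matching SAP text. No new data, visits or patients are needed, and the sample size can stay as it is.

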### 5.2 Secondary Endpoints

#### Efficacy

- New syndesmophyte formation or progression of existing syndesmophytes after 2 years of treatment.
- Improvement of disease activity, function, axial mobility and quality of life measures at Week 12 and Week 108 in comparison to baseline according to:
  - BASDAI
  - ASDAS
  - CRP and erythrocyte sedimentation rate (ESR)
  - Bath AS Functional Index (BASFI)
  - Bath AS Metrology Index (BASMI) and chest expansion
  - Global assessment (patient/physician), general pain and nocturnal pain on the numeric rating scale (NRS)
  - ASAS Health Index
  - Physician Acceptable Symptom State (PhASS)
  - Patient Acceptable Symptom State (PASS)
  - Percentage of subjects who achieve an ASAS20, ASAS40, ASAS partial remission, BASDAI50 and ASDAS in comparison to baseline;
- Change of soluble and cellular biomarkers of inflammation and bone / cartilage turnover at week 108 in comparison to baseline and their relevance for the prediction of radiographic progression.
- Change of the enteric microbiome profile at week 108 in comparison to baseline.
- Change of osteitis score and scores for the chronic post-inflammatory changes in the spine and sacroiliac joints (SIJ) on magnetic resonance imaging (MRI) by Berlin MRI

scoring method at week 108 in comparison to baseline – for the MRI sub-study patients only.

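### The p < 0.05 rule in section 13.5 is not limited to the primary test, so it also covers about 20 unordered secondary comparisons; those p values should be called nominal

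*Protocol*

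**What the plan says.** The primary analysis is well defined. Sections 5.1, 13 and 13.5 name one endpoint (change in mSASSS), one population (ITT, with multiple imputation) and one test (Mann-Whitney). Section 13.8 sizes the trial on that contrast alone, at two-sided 0.05.

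The secondary endpoints in 5.2 are numerous. They start with a structural one, "New syndesmophyte formation or progression of existing syndesmophytes after 2 years of treatment". A list of clinical measures follows, in which a single line can hold several outcomes, such as "Global assessment (patient/physician), general pain and nocturnal pain on the numeric rating scale (NRS". The clinical list ends with "Percentage of subjects who achieve an ASAS20, ASAS40, ASAS partial remission, BASDAI50 and ASDAS in comparison to baseline". Biomarkers, the microbiome and, in a sub-study, MRI scores complete the section.

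These endpoints are to be tested between arms. The synopsis states: "Mann-Whitney U-test, linear mixed models, and Chi-square test will be used in order to evaluate differences in the secondary outcome parameters between treatment groups". Section 13.5 adds that mixed models "will be applied to compare means of secondary outcome parameters over time", and then: "Nonresponder imputation for missing response data and chi-square tests will additionally be applied to compare response rates". The next and last sentence of 13.5 is the rule: "Two-sided p values < 0.05 will be considered to be statistically significant".

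**The concern.** The rule has no qualifier and directly follows a sentence about secondary response rates, in a section that deals mostly with secondary analyses. The alpha of the primary test is already set in 13.8. The natural reading is therefore that every efficacy p value below 0.05 is to be called statistically significant. Nothing in the protocol ranks the secondaries, makes them conditional on the primary, divides alpha among them or calls them exploratory.

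What is at stake is how secondary results are described, above all if the mSASSS comparison is null. The trial is open-label, and blinded assessment is described only for the spinal radiographs. Most of the clinical secondaries are reported by the patient or the physician. Under the rule as it stands, a chance difference in any of them could be reported as a statistically significant effect of adding celecoxib. The secondary closest to the study objective, syndesmophyte formation or progression, has no priority over the rest.

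**Working it through.** **The plan's own figure.** Section 13.8 gives 38 per group for the primary test. With a Welch t-test, difference 1.5, SDs 2.8 and 1.6 and two-sided 0.05, power is 80.5% at 38 per group and 79.4% at 37. The stated 38 reproduces. The whole 0.05 is spent on one primary test, so the level of that test is not in question. The protocol states no family-wise error rate for the secondaries, so there is no figure of that kind to reproduce.

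**Counting the secondaries (5.2, week 108).**

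- Structural: syndesmophyte formation or progression = 1.
- Clinical measures: BASDAI, ASDAS, CRP, ESR, BASFI, BASMI, chest expansion, patient global, physician global, general pain, nocturnal pain, ASAS Health Index, PhASS, PASS = 14.
- Response rates: ASAS20, ASAS40, ASAS partial remission, BASDAI50, ASDAS = 5.
- Total: 1 + 14 + 5 = 20.

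If one biomarker, one microbiome comparison and four MRI scores are assumed (osteitis and chronic change, each for spine and sacroiliac joints), the count is 20 + 1 + 1 + 4 = 26. Week-12 comparisons are left out because randomisation takes place at that visit. Safety comparisons are not counted.

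**False positives when every secondary null is true.**

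- Expected number: 20 × 0.05 = 1.0, or 26 × 0.05 = 1.3, whatever the correlation.
- At least one in either direction, independent tests: 1 − 0.95^20 = 64.2%; 1 − 0.95^26 = 73.6%.
- At least one falsely favouring celecoxib, independent tests: 1 − 0.975^20 = 39.7%; 1 − 0.975^26 = 48.2%.

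The tests are not independent. The protocol gives no correlations, so a common correlation ρ among the test statistics is assumed. With z_i = √ρ·c + √(1−ρ)·e_i, where c and e_i are standard normal, a result counts as significant in either direction when |z_i| > 1.96, and as favouring celecoxib when z_i > 1.96.

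| Assumed ρ | 20 tests, either direction | 20 tests, favouring celecoxib | 26 tests, either direction | 26 tests, favouring celecoxib |
|---|---|---|---|---|
| 0 | 64% | 40% | 74% | 48% |
| 0.3 | 54% | 28% | 62% | 32% |
| 0.5 | 42% | 21% | 48% | 24% |
| 0.7 | 29% | 14% | 32% | 16% |
| 0.8 | 22% | 11% | 24% | 12% |

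Several outcomes overlap by construction: BASDAI with BASDAI50, ASAS20 with ASAS40, and ASDAS as a mean and as a response. CRP and ESR, and the pain and global scores, are also likely to move together. The rows from 0.3 to 0.8 are therefore the more realistic ones.

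**The case against.** **This belongs in the SAP.** The handling of secondary multiplicity is commonly left to a separate plan, and section 13.3 shows that one is intended. This stands as far as it goes: the absence of a hierarchy is not a finding in itself. However, section 13 is itself headed as the statistical analysis plan, and the only item it expressly defers is the list of reasons for per-protocol exclusion. The significance rule is stated, not deferred. A later plan that treats the secondaries as exploratory would have to depart from 13.5.

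**The sentence is an ordinary per-test level.** It promises no family-wise control. The protocol already separates one primary endpoint from the secondaries, and no passage lets a secondary replace a failed primary. This is correct. It confines the point to the wording of secondary claims and keeps it minor.

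**Stronger readings a reader might infer.**

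- That a false celecoxib benefit is likely. It is not: the chance is below 50% in every case computed, and 11% to 28% for 20 tests at assumed correlations of 0.3 to 0.8. Even counting both directions, 20 tests exceed 50% only when correlation is weak.
- That testing the same construct twice makes matters worse. Overlap raises correlation, and that lowers the chance of any false positive.
- That the primary conclusion is weakened. It is not.

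**The global null may be false.** Section 4.3.1 allows NSAIDs a symptomatic effect, so some differences in pain or BASDAI could be real. This also stands: the percentages describe the case in which celecoxib affects none of the outcomes. Nor would multiplicity control remove reporting bias from the open-label design. That is a separate reason for caution with these outcomes.

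**Conclusion.** The point holds as a minor one. The rule in 13.5 is broader than it needs to be: as written, it allows about 20 unordered secondary comparisons to be called statistically significant one at a time. If none were affected by celecoxib, one false-positive result would be expected on average. The size rests on three assumptions: 20 tests, all nulls true, and equal correlations between 0.3 and 0.8 that the protocol does not supply. The count could be higher with MRI scores, several biomarkers or repeated time-by-group contrasts. The primary test, the sample size and the conduct of the trial are unaffected.

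**What to change.** In 13.5, replace the last sentence with a rule of this kind, and repeat it in the synopsis:

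> The two-sided 0.05 significance level applies to the primary Mann-Whitney comparison of mSASSS change. All secondary comparisons are reported as estimates with 95% confidence intervals and nominal p values, without claims of statistical significance.

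Optionally, syndesmophyte formation or progression could be tested at two-sided 0.05 only if the primary is significant. That is one acceptable scheme among several and is not required to resolve the point.

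The cost is one or two sentences before database lock, with no added patients or procedures. The downside is that clinical, MRI, biomarker and microbiome results can no longer be called statistically significant. If a separate SAP already says this, only the protocol wording needs to be aligned with it.
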